## **1.0 Project Summary/Abstract**

Many African-Americans and Latinos with diabetes do not achieve recommended diabetes goals placing them at high risk for complications. Team-based models of care can help in reaching goals of therapy. Additionally, mobile health (mHealth) technologies can further improve outcomes among those more difficult to reach. This study will evaluate the impact of a team-based, mHealth intervention designed to improve medication adherence, healthy eating, and physical activity behaviors. We will compare this mHealth approach with usual care.

Clinical pharmacists and health coaches (HC) will deliver our proposed team-based intervention. mHealth delivery includes mobile phone text messaging, secure videoconferencing, and HC home visits. Pharmacists will focus on medication reconciliation and adherence. Health coaches will help identify psychosocial and environmental challenges to adherence in a culturally-sensitive manner. Together, they can assist in goal-setting, problem-solving, negotiation of competing priorities, and provide social support leveraging mHealth technologies.

Preliminary data from our research group supports the role of health coaches partnering with clinic-based pharmacists in improving diabetes outcomes in minorities. In the proposed mHealth intervention, patient-pharmacist videoconferencing will eliminate the need for in-person visits with a pharmacist, which is impractical for many low-income patients. In addition, our pilot work suggests that text messaging is a preferable means of communication and may facilitate more frequent contact with patients.

We propose a randomized, controlled trial to evaluate the effectiveness of an mHealth diabetes adherence support intervention delivered by clinical pharmacists and health coaches. We will randomize 220 patients through UI Health to either: (1) mHealth diabetes adherence support through clinical pharmacists and health coaches; or (2) usual care. After one year, patients completing the mHealth intervention will be monitored for an additional year while the usual care group receives the mHealth approach. Outcomes include medication adherence, hemoglobin A1c, blood pressure, and LDL-cholesterol levels. The specific aims include: (1) evaluate the effectiveness of an mHealth diabetes adherence support intervention delivered by clinical pharmacists and health coaches to African-American and Latino adults with uncontrolled type 2 diabetes; (2) evaluate the maintenance of improved diabetes behaviors as well as clinical outcomes one year after completing the intervention; (3) evaluate the cost and cost-effectiveness of mHealth diabetes adherence support compared to usual care; and (4) evaluate the reach, adoption, and implementation of mHealth diabetes adherence support based on the RE-AIM framework.

### **1.1 Project Summary for the mDAS Sleep Sub-study Supplement**

As part of the parent R01 described above, [name] will conduct a smaller sub-study that is funded with a diversity supplement award to the R01. The award supports [name] gaining structured and unstructured experiences in research training over two years. With support of a mentored research study, she will investigate mobile health (mHealth) evaluation of sleep within the context of Type 2 diabetes. Sleep quality and duration are

modifiable risk factors that can help people improve diabetes control and reach diabetes goals. Although poorly understood, African-Americans and Latinos often report poorer sleep quality and/or duration and may be more susceptible to the metabolic effects of poor sleep. Additional research is needed to understand sleep behaviors and the possible impact on the health and well-being of these populations. Currently, sleep is rarely assessed by clinicians and behavioral interventionists. mHealth technologies can potentially improve the evaluation and study of sleep in these populations. This study will characterize sleep (quality, duration, and patterns) among African-Americans and Latino-Americans with uncontrolled diabetes, evaluate the effectiveness of mHealth in monitoring sleep and explore the relationships between sleep and diabetes outcomes. mHealth exploration includes mobile phone text messaging, wrist actigraphy use, and self-report surveys of sleep. Preliminary data from this study will inform the development of remotely-delivered approaches to sleep assessment and intervention (e.g., promotion of sleep hygiene). Initially, [name] will lead a cross-sectional study of 40 participants to assess and explore the impact of sleep using mHealth.

The specific aims of this proposed study include: (1) explore subjective daily sleep quality, duration, and pattern of 40 inner-city African-American and Latino-American patients with poorly controlled type 2 diabetes (hemoglobin A1c>8%); (2) evaluate the feasibility and acceptability of objectively measuring sleep quality, duration, and patterns and sedentary behaviors via mHealth; and (3) explore the relationships between subjective and objective measures of sleep quality, duration, and patterns, as well as the relationship between sleep measures and glycemic control (i.e., hemoglobin A1c), quality of life, depression, and sedentary behaviors. Ultimately, this research may help demonstrate a potential role of mHealth evaluation of sleep, leading to innovative, behavioral strategies to improve diabetes-related outcomes.

## **2.0 Background/Scientific Rationale**

Diabetes affects approximately 13% of African-American and Latino adults in the United States. Aggressive management of blood glucose, blood pressure, and cholesterol through medication and lifestyle adherence are necessary to minimize adverse health outcomes. However, barriers to adherence contribute to the fact that fewer than 20% of these ethnic minorities actually reach all therapeutic goals. As a result, improvement in minority diabetes management remains a priority for research.

Medical nutrition therapy, physical activity, and pharmacotherapy are essential components of diabetes self-management. Adherence to diet and physical activity is low for a majority of Americans including those with type 2 diabetes. Similarly, adherence to medication is poor: 20-30% of prescriptions are never filled, and 50% of medications for chronic disease are not taken as prescribed. Self-management among low-income, minority populations is often more problematic due to extensive barriers such as low health literacy, depression, lack of social support, poor patient-clinician communication, and limited access to healthcare. Latinos may face additional barriers such as low English proficiency and other cultural issues. Low adherence may reduce treatment modifications and intensification contributing to poor diabetes control. Systematic reviews of interventions designed to

improve medication adherence found few studies that improved clinical outcomes. Sample sizes were small, and minorities (especially Latinos) were underrepresented. Further research is necessary to identify effective interventions that improve adherence in ethnic minority populations.

The *patient-centered medical home* (PCMH) approach has been endorsed widely and involves diverse health professional teams working collaboratively with primary care physicians to provide high levels of care, access, communication, care coordination and integration.

*Clinical pharmacists* improve glycemic control in diabetes management with their expertise in medication management and ability to adjust therapy in collaboration with providers. Clinical pharmacists are widely accepted in this role; most state boards of pharmacy authorize collaborative drug therapy management protocols between clinical pharmacists and prescribers. For example, Project IMPACT: Diabetes is a national research initiative supporting pharmacists working in community-based diabetes care teams, involving 25 underserved communities across the U.S. Pharmacist-led interventions enhance adherence to chronic disease medication through patient education, use of adherence aids, and addressing medication-related issues (e.g., drug interactions and cost). Our research with low-income minority patients suggests that in-person pharmacist visits are not feasible for many patients due to the added travel burden, cost, and time from work. Also, few studies of pharmacist-based models of care have included Federally Qualified Health Centers (FQHCs) or focused on low-income minority populations.

*Health coaches* (HCs) are increasingly included as members of the medical home for vulnerable groups as their involvement contributes to improvement in diabetes self-management and A1c levels. The Patient Protection and Affordable Care Act (ACA) formally recognizes the role of HCs in health promotion and education, disease management, patient navigation, improving health literacy, and advocacy. UI Health has representation on the Illinois Department of Public Health (IDPH) Community Health Worker Advisory Board to support implementation across Illinois. Trained HCs are trusted by patients, understand socio-cultural barriers, and can help increase the relevancy of disease self-management to individuals who are struggling to manage competing priorities. Our research demonstrates that HCs can successfully collaborate with clinical pharmacists in addressing lifestyle and medication adherence.

Mobile health (mHealth) includes “the use of mobile computing and communication technologies in health care and public health.” Our mHealth approach includes tablet computer videoconferencing and cell phone text messaging components.

While the presence of mHealth applications is exploding in healthcare, few studies have explored the impact of videoconferencing on chronic disease management. Systematic reviews of Internet-mediated communication technologies fail to show clear effects on health due to variation in study design and technologies, heterogeneous study populations, and variability in contact frequency. In diabetes care, technology-based interventions focus on transmission of blood glucose values with less attention on addressing barriers to self-management. Empirical data suggest that videoconferencing in diabetes care is practical, potentially cost-effective, and reliable for disease management. Video conferencing with clinical pharmacists to promote medication adherence is a growing model in rural practice (e.g., Department of Veterans Affairs and Kaiser Permanente) but not well studied, particularly with mobile devices

or involving urban, low-income minority patients. Our study will focus on low-income African-Americans and Latinos and explore the use of videoconferencing between patients and clinical pharmacists, facilitated by HCs.

Text messaging interventions in diabetes management have shown mixed results and inclusion of low-income minorities has been low. Few formal randomized controlled studies of text messaging exist. One recent study showed short-term, modest improvement in cardiovascular risk factors in Australians with coronary heart disease. While there are no clear, specific intervention components shown to improve outcomes, follow-up contact, individualized frequency, and tailored support likely improve acceptability and responsiveness by users. Our study will include daily, tailored text messages with HC follow up to provide social support, improve self-efficacy, and adherence. Furthermore, the proposed study utilizes inexpensive technologies for text messaging and video conferencing, with greater potential for widespread adoption in underserved communities.

The widespread use of cell phones and text messaging among low income and minority populations has allowed HCs to increasingly adopt technology in their work. To date, most of this research has been conducted outside of the U.S. utilizing technology for field-based data collection, sending reminders, providing health education, and communication. Within the U.S., integration of low-cost technologies into community-based HC interventions remains an emerging area of research.

Despite widespread use of mobile devices, little is known about the effectiveness of the technology to improve health care delivery or outcomes. Systematic reviews show preliminary value of text messaging, patient education apps, and videoconferencing in chronic disease management, but most studies have been small in size, underpowered, low in quality, and include motivated, non-minority subjects. Our work will provide needed evidence on the impact of mHealth diabetes adherence support delivered to low-income minority patients with uncontrolled diabetes.

## **2.1 Background/Scientific Rationale for mDAS Sleep Sub-study Supplement**

Diabetes is a leading cause of death and disability in the US costing \$45 billion in direct medical costs and reduced productivity. Diabetes disproportionately affects minority populations especially African-Americans and Latino-Americans. Studies have shown that lifestyle intervention can reverse and/or improve diabetes control. While healthy eating and physical activity are well-studied behaviors in diabetes self-management, sleep is increasingly being recognized as a potential modifiable factor that can also lead to increased diabetes control. Studies have shown that people with short sleep duration, long sleep duration, or poor quality sleep have worse glycemic control, even without sleep-disordered breathing such as obstructive sleep apnea. Poor sleep quality and duration can lead to weight gain and impaired glucose tolerance. For these reasons, sleep is an essential lifestyle component to study in diabetes self-management.

It is well established that African-Americans, Latinos, and other ethnic and racial minorities are more likely to develop diabetes and develop complications from the disease. It is possible that poor sleep duration and quality contribute to these health disparities. Data

exploring sleep quality within minority populations is very limited. However, existing data suggest that African-Americans are more likely to have worse sleep quality and shorter sleep duration compared to whites, whereas Latinos are more likely to have shorter sleep duration compared to whites. Additional research is needed considering that these groups are also more likely to report psychosocial stress that contributes to inconsistent sleep patterns. Furthermore, these populations are more likely to have nonstandard and non-day work hours (e.g., shift work) that contribute to inconsistent sleep and an increased risk of diabetes. Further sleep research involving minority populations with diabetes is strongly justified and long overdue.

Despite evidence supporting a strong relationship between sleep and glycemic control, the mechanisms underlying the link are not well understood. Both diabetes and poor sleep are associated with more depression, lower quality of life, and more sedentary behavior. In addition, socio-environmental factors secondary to poverty (e.g., neighborhood violence, social isolation, etc.) may result in higher levels of chronic stress that contribute to the link. The proposed study will explore these pathways by collecting detailed subjective and objective sleep assessments in patients with diabetes in addition to depression, quality of life, and physical activity (which are assessed in the parent grant). This study will begin to provide a nuanced understanding of the complex relationships between these highly relevant variables.

Little is known about the utility of mHealth to objectively evaluate sleep. The gold standard for studying sleep is polysomnography. Unfortunately, this method is cumbersome and not feasible in a real-world setting. mHealth devices provide an opportunity to evaluate sleep in a natural setting. This is particularly valuable in mHealth intervention studies, including the parent study, where mobile assessments and interventions are incorporated. A few popular low-cost commercial activity trackers (e.g., Fitbit and Garmin) are widely available, however, they overestimate polysomnography total sleep time and sleep onset latency or underestimate wake after sleep onset. Alternatively, wrist actigraphs represent evidence-based activity trackers that serve as comparable alternatives to polysomnography for measurement of sleep in the home. Actigraphs provide accurate measures of total sleep time, sleep percentage, movement, and wake after sleep onset. In addition, their value may further improve with supplementary data from text message-prompted sleep diaries and selected questionnaires. Together, the mHealth and traditional approaches can be used to evaluate home sleep environments and support efforts to develop sleep interventions.

The overall objectives of this supplement are to evaluate the feasibility and acceptability of mobile health approaches to assessing sleep duration and quality within minority populations known to have poor control of their type 2 diabetes. We will explore the relationships between sleep (duration, quality, and patterns), glycemic control, depression, quality of life, and sedentary behavior. Findings from this study will provide critical preliminary data to support [name] application for a career development award. [name] goal is to establish an on-going line of research as an independent investigator focused on developing sleep hygiene interventions to improve sleep duration and quality in minority populations with diabetes.

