### 3.1 Objectives/Aims for mDAS Sub-study Sleep Supplement

Sleep quality and duration are increasingly being recognized as modifiable risk factors for improving diabetes control. Studies have shown that short sleep duration (less than 7 hours), long sleep duration (more than 8 hours), and poor quality of sleep are associated with impaired glucose tolerance and insulin resistance. This increases the risk of developing diabetes and worsens glycemic control among those with type 2 diabetes. Research specifically targeting sleep among low-income African-Americans and Latinos is lacking; however, available data suggest that these groups are more likely to experience problematic sleep patterns resulting in detrimental metabolic effects of poor sleep. In addition, clinicians rarely assess sleep, though they are available to intervene on sleep hygiene. Collectively, these factors support the need to further investigate sleep in low-income minority populations with diabetes with intentions of developing remotely-delivered sleep assessment and intervention. The overall objectives of this study are to characterize sleep quality and duration among African-Americans and Latino-Americans with uncontrolled diabetes, evaluate the effectiveness of mHealth in monitoring sleep quality and duration, and explore the relationships between sleep and glycemic control.

The specific aims of this proposed study include:

**Aim 1:** To explore subjective daily sleep quality, duration, and patterns of 40 inner-city African-American and Latino-American patients with poorly controlled type 2 diabetes (hemoglobin A1c $\geq$ 8%). Sleep quality, duration, and patterns will be measured by a validated sleep questionnaire, a mHealth version of a validated consensus sleep diary, and a home sleep environment questionnaire.

**Aim 2:** To evaluate the feasibility and acceptability of objectively measuring sleep quality, duration, and patterns and sedentary behaviors via mHealth. Study participants will wear an Actigraph Watch for seven days (including nights) and report their experiences with the device and assess its acceptability.

**Aim 3:** To explore the relationships between subjective and objective measures of sleep quality, duration, and patterns, as well as the relationships between the sleep measures, glycemic control (i.e., hemoglobin A1c), quality of life, depression, and sedentary behaviors.

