Hypotheses 3a: Poorer sleep quality, duration, and patterns will be associated with higher hemoglobin A1c levels.

Hypotheses 3b: Poorer sleep quality, duration, and patterns will be associated with a lower quality of life, depression and more sedentary behaviors.

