### **Additional text messaging for mDAS Sub-study Supplement**

Participants in the sub-study will be asked to answer daily questions on their previous night's sleep. They will complete the seven day sleep assessment surveys based on their preference by either text message surveys using myTapp or they will receive a text link to an online-based survey through a secure, web-based data collection application, such as REDCap or Qualtrics. The text messages will serve as a modified mobile consensus sleep diary for patients during the sleep period. The questions will include the following:

- 1) What time did you get into bed last night?
- 2) What time did you try to go to sleep?
- 3) How long did it take you to fall asleep?
- 4) How many times did you wake up, not counting your final awakening?
- 5) In total, how long did these awakenings last?
- 6) What time was your final awakening?
- 7) What time did you get out of bed for the day?
- 8) How would you rate the quality of your sleep? a) very poor, b) poor, c) fair, d) good, or e) very good? Please text the letter that corresponds to you (if using text message response).
- 9) In total, how long did you nap or doze?
- 10) Comments

Thanks for your participation.

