## 12.1 Additional Statistical Considerations for mDAS Sub-study

[name] will receive statistical/analytic support from the Methodology Research Core at the Institute for Health Research and Policy (IHRP) and statistician [name]. Descriptive statistics will be summarized as mean (standard deviation) or median (range) for continuous variables, and as frequencies (proportions) for categorical variables. We will address the three specific aims as follows:

**Aim 1:** Descriptive statistics will be calculated for the PROMIS as well as sleep duration based on text-message responses. Response rates will be quantified per individual and overall in aggregate. Interviews will provide an inventory of potential barriers to sleep in the home (e.g., presence of television in bedroom). These will be categorized and quantified. Differences in race/ethnicity within the descriptive data will also be compared.

**Aim 2:** Feasibility and acceptability of using the Actiwatch to collect objective sleep data will be based on the average number of days and amount of time per day the Actiwatch was worn. In addition, research personnel will obtain qualitative information regarding barriers to wearing the device in the semi-structured phone interview. Drs. [name], [name], and [name] will collaboratively determine a coding scheme to describe issues discovered.

**Aim 3:** Independent and dependent variables will be explored via histograms to identify extreme values and assess normalcy (some Actiwatch data may yield spurious values). We will determine correlations between subjective text-message sleep diary and objective Actiwatch data (e.g., total sleep time and bouts of waking after sleep onset). In addition, we will examine correlations between sleep parameters (e.g., total sleep time) and hemoglobin A1c, depression, quality of life, and sedentary behavior. For continuous variables, Pearson correlations will be calculated (and Spearman rank for non-parametric variables). Partial correlation models will include covariates such as patient age, gender, race/ethnicity, income, and education level. We will explore additional models that include the number of days the Actiwatch device was worn. All hypothesis tests will be 2-sided with a significance level of 0.05.

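### Sleep sub-study: the previous-night diary has no rule for a main sleep taken by day, and section 12.1 specifies no measure of sleep 'patterns' or of daily quality

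*Protocol*

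**What the plan says.** **Rationale.** Section 2.1 gives several reasons to study sleep: short, long or poor-quality sleep and glycemic control; psychosocial stress ("these groups are also more likely to report psychosocial stress that contributes to inconsistent sleep patterns"); and work hours ("these populations are more likely to have nonstandard and non-day work hours (e.g., shift work) that contribute to inconsistent sleep"). Section 7.0, under the additional benefits of the sub-study, again pairs stress with non-standard hours as sources of inconsistent sleep.

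**Aims and hypotheses.** Aim 1 in section 3.1 is "To explore subjective daily sleep quality, duration, and patterns of 40 inner-city African-American and Latino-American patients". Hypothesis 3a reads "Poorer sleep quality, duration, and patterns will be associated with higher hemoglobin A1c levels". Hypothesis 3b uses the same three sleep constructs against quality of life, depression and sedentary behavior.

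**Instruments.** Sections 5.1 and 6.1 and the sub-study text-messaging section all frame the diary as the night before; the last says "Participants in the sub-study will be asked to answer daily questions on their previous night's sleep". Item 1 is "What time did you get into bed last night". Items 2 to 7 ask for clock times, latency and awakenings, item 8 for a quality rating, item 9 for total nap or doze time and item 10 for comments. Under section 6.1, answers are given after waking and the Actiwatch is worn for 7 days and 7 nights.

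**Covariates.** Section 8.0 lists employment status. Neither section 8.0, the sleep surveys in section 6.1 nor the covariates named in section 12.1 include a work schedule.

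**Analysis.** For Aim 1, section 12.1 states: "Descriptive statistics will be calculated for the PROMIS as well as sleep duration based on text-message responses". It adds response rates, barriers to sleep in the home and a comparison by race/ethnicity. For Aim 3 it names total sleep time and bouts of waking as examples.

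**The concern.** Two gaps appear when these sections are read together.

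First, the protocol expects some participants to work non-day hours, yet it asks everyone about the preceding night. Someone who came off a night shift and slept from morning to afternoon has no instruction on where that sleep belongs. It could go into items 1 to 7, into the nap item, or nowhere. The Actiwatch records it regardless, so the two instruments could describe different periods. Aim 3 correlates them, and a low correlation could then reflect wording rather than poor recall or a poor device. Without a work-schedule item, the people affected cannot be reliably identified afterwards.

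Second, patterns is a named construct in the aims and a predictor in two hypotheses, but section 12.1 does not say what variable represents it or what makes a pattern poorer. Aim 1 speaks of daily quality, yet the nightly rating in item 8 has no stated analysis. With 40 people and several possible summaries, a measure chosen after seeing the data would weaken what is meant to be preliminary evidence.

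**Working it through.** The protocol gives no power, precision, standard deviations or share of day sleepers for the sub-study, so there is no planned figure to reproduce. The check is textual, with arithmetic for scale only.

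**1. Constructs against stated analysis**

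| Construct in the aims | Data planned | Analysis named in 12.1 |
|---|---|---|
| Duration | Diary items 2 to 6, Actiwatch | Yes (Aims 1 and 3) |
| Quality | PROMIS at entry; item 8 daily | PROMIS yes; item 8 none |
| Patterns | Diary clock times (items 1, 2, 6, 7), Actiwatch | None by name |

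The Aim 1 list carries no 'e.g.'; the Aim 3 lists do.

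**2. Diary frame.** Only item 1 contains the words 'last night', but it opens the sequence and the introduction sets the same frame. A main sleep by day is recovered if the participant reads items 2 to 7 as the latest sleep. It is separated from main sleep if entered under item 9, and lost if not entered.

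**3. Size of the possible loss (all inputs assumed).** Take Actiwatch sleep *T* as true, mean 6.5 h, SD 1.2, and diary *D* = *T* + error with SD 0.9. Then Var(*D*) = 1.44 + 0.81 = 2.25, and the baseline correlation is 1.2/1.5 = 0.80. Let a share *p* of participants be day sleepers who lose a fraction *c* of their main sleep from the diary:

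- Var(*H*) = 44.5 × [1 − *p* + *p*(1 − *c*)²] − [6.5(1 − *cp*)]², where 44.5 = 2.25 + 6.5²
- correlation = (1 − *cp*) × 1.2 / √Var(*H*)
- shift in mean diary sleep = −6.5*cp*

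Example, *p* = 0.10 and *c* = 0.5: Var(*H*) = 44.5 × 0.925 − 6.175² = 41.16 − 38.13 = 3.03; correlation = 0.95 × 1.2/1.741 = 0.65; shift = −0.33 h.

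| Day sleepers | Nothing lost | Half lost | All lost |
|---|---|---|---|
| 5% (2 of 40) | 0.80, 0 h | 0.72, −0.16 h | 0.56, −0.33 h |
| 10% (4 of 40) | 0.80, 0 h | 0.65, −0.33 h | 0.45, −0.65 h |
| 20% (8 of 40) | 0.80, 0 h | 0.57, −0.65 h | 0.33, −1.30 h |

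**4. Sensitivity to method.** A simulation with n = 40, sleep SD 1.0 and a baseline Pearson correlation of 0.59 placed 2, 4 or 6 people at 0 to 2 h on every diary day. Pearson fell to 0.36, 0.27 and 0.23. Spearman, which section 12.1 also provides for, fell from 0.56 to about 0.50, 0.45 and 0.40. If only three of the seven days were affected, Pearson was about 0.51, 0.47 and 0.43.

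**5. What a patterns measure could deliver.** With 7 nights (6 degrees of freedom, independent normal nights assumed), the 95% interval for one person's SD runs from √(6/χ²₀.₉₇₅) = 0.64 to √(6/χ²₀.₀₂₅) = 2.20 times the estimate. With n = 40, two-sided 0.05 and 80% power, the detectable correlation is tanh(2.80/√37) = 0.43, or tanh(2.80/√32) = 0.46 with the five covariates named, each counted as one term. The measure is usable for exploration but noisy.

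**The case against.** The strongest reply is that the protocol already copes. Six of the seven timing items do not mention night, answers are given after waking, naps and comments are captured, and the Actiwatch covers all 24 hours. A sensible day sleeper would report the sleep just finished, and nothing would be lost. The choice of regularity index in an exploratory study is also a detail that an analysis plan may properly hold. Much of this stands, and it rules out several stronger readings that a reader might infer:

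- *That the sub-study is built on shift work.* It is one rationale among several in section 2.1.
- *That day sleepers are mis-scored.* No section shows this; the wording only leaves it to chance.
- *That patterns will never be estimated.* The Aim 3 lists are examples, and the data support a measure.
- *That sleep-A1c findings will be spurious.* Adding an assumed A1c difference of 1.0 for day sleepers raises Pearson rejection from 5% to 8%, 14% and 20% with 2, 4 and 6 of them. The protocol gives no such difference. Spearman gives about 5.5%, 7.6% and 11.5%, and Actiwatch sleep stays near 5%.
- *That day sleepers would be screened out.* Variables are to be "explored via histograms to identify extreme values and assess normalcy (some Actiwatch data may yield spurious values"). The spurious-value remark concerns the Actiwatch, which records day sleep, and the text speaks of identifying values, not removing them.

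Two things survive. The diary wording is printed in the protocol, so an analysis plan cannot repair it. And section 12.1 sets out its own aim-by-aim analysis, in which the Aim 1 list omits timing and item 8.

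**Conclusion.** The point holds as a low-priority improvement. The diary frame leaves a main sleep by day without a place, work schedule is not collected, and section 12.1 names no timing or regularity measure and no analysis of item 8. The effect on the diary-Actiwatch comparison ranges from none to a clear fall: under the assumptions above, from 0.80 to between 0.33 and 0.72 for 5% to 20% day sleepers losing half or all of their diary main sleep. The upper end requires day sleep throughout the week with nothing recovered from the nap item, so it is close to a worst case. None of these inputs comes from the protocol. The sub-study is exploratory and cross-sectional, with 40 participants, and nothing here touches the 220-patient comparison.

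**What to change.** 1. Reword the diary introduction and item 1 to refer to 'your main sleep period in the past 24 hours', so that items 2 to 7 follow that frame and item 9 covers sleep outside it. Score the Actiwatch on the same period.
2. Add one item on work schedule during the recorded week.
3. In section 12.1, name the within-person SD over the 7 days of sleep and wake times (diary items 2 and 6 and the Actiwatch equivalents) as the patterns measure, with larger values meaning poorer. Compute it so that times either side of midnight are treated as close. Name the mean of item 8 as daily quality. Use both for Aim 1 and hypotheses 3a and 3b.

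**Cost.** A wording change to a diary that is already modified, one extra question, and summaries of data already planned. The diary moves slightly further from its source wording, and answers collected under the present wording need a flag in the analysis.
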